## Abstract

**Background:**

Cholera remains a serious public health problem in low-income countries despite efforts in the past to promote oral rehydration therapy as major treatment. In 2007, the majority of worldwide cases (94%) and deaths (99%) were reported from Africa. To improve cholera control efforts in addition to maintaining and improving existing water supply, sanitation and hygiene behaviour measures, the World Health Organization has recently started to consider the use of vaccines as an additional public health tool. To assess this new approach in endemic settings, a project was launched in Zanzibar to vaccinate 50,000 individuals living in communities at high risk of cholera with an oral two-dose vaccine (Dukoral^®^).

Immunisation programmes in low-income countries have suffered a reduced coverage or were even brought to a halt because of an ignorance of local realities. To ensure the success of vaccination campaigns, implementers have to consider community-held perceptions and behaviours regarding the infectious disease and the vaccine of interest.

The main aim of this study is to provide advice to the Ministry of Health and Social Welfare of Zanzibar regarding routine introduction of an oral cholera vaccine from a socioeconomic and behavioural perspective as part of a long-term development for a sustained cholera prevention strategy.

**Methods and design:**

Qualitative and quantitative methods of health social science research will be applied on four stakeholder levels before and after the mass vaccination campaign. Rapid assessment individual interviews and focus groups will be used to describe cholera- and vaccine-related views of policy makers, health care professionals and community representatives. The cultural epidemiological approach will be employed on the individual household resident level in a repeated cross-sectional design to estimate determinants of anticipated and actual oral cholera vaccine acceptance.

**Discussion:**

The study presented here is designed to inform about people's perceptions regarding cholera and about socioeconomic and behavioural factors determining anticipated and actual oral cholera vaccine acceptance in Zanzibar. Its pre- and post-intervention design using a mixed-methods approach on different stakeholder levels in communities at high risk of cholera outbreaks will ensure the collection of locally valid data relevant for public health action and planning.

## Background

### Etiology, symptoms and treatment of cholera

Cholera is an intestinal disease caused by the bacterium *Vibrio cholerae *which spreads mainly through faecal contamination of water and food by infected individuals [1]. Eating raw or undercooked seafood can also cause the infection since *V. cholerae *was found on phyto- and zooplankton in marine, estuarine and riverine environments independent of infected human beings [2,3]. Two out of ca. 240 serogroups of *V. cholerae *– O1 and O139 – are pathogenic. The O1 serogroup can further be subdivided into two biotypes – classical and El Tor.

After an incubation period of 18 hours to five days, infected individuals will develop acute watery diarrhoea. Large volumes of rice-water-like stool and concurrent loss of electrolytes can lead to severe dehydration and eventually death if patients are not rapidly treated. Most of the infected individuals, however, are asymptomatic or suffer only from mild diarrhoea. An inoculum of 10^8 ^bacteria is needed in healthy individuals to cause severe acute watery diarrhoea while a 1,000-fold lower dose is sufficient to cause the disease when gastric acid production is reduced. Other clinical features besides profuse diarrhoea (more than three loose stools per day) to establish a cholera diagnosis include abdominal and muscle cramps and frequent vomiting [4]. Without treatment the case-fatality rate (CFR) can reach 50% [1].

Treatment of cases depends on the severity and includes i) giving oral rehydration solutions (ORS) after each stool if no dehydration is apparent, ii) giving ORS in larger amounts if moderate dehydration is apparent, and iii) using intravenous drips of Ringer Lactate or saline for severely dehydrated patients [4]. Antibiotics can be administered to shorten the episode in severe cases.

### Prevention of cholera

Cholera usually occurs in epidemics and can cause major disruptions in affected health systems as rigorous measures have to be taken and patients treated in camps under quarantine-like conditions. Outbreaks of cholera can easily be prevented by providing safe water, sanitation and promoting good personal hygiene behaviour and safe food handling. Regions where such control measures have not been realised, or where maintenance and monitoring of existing schemes is not guaranteed, are at greatest risk of epidemics and consequently could become endemic with cholera.

The World Health Organization (WHO) has recently started to consider the use of vaccines as an additional public health tool to control cholera in low-income countries since the implementation of the above-mentioned prevention and control measures has not had the desired impact on cholera incidence [5]. Currently only one safe and efficacious vaccine is available on the market – Dukoral^® ^– an oral cholera vaccine (OCV) consisting of killed whole-cell *V. cholerae *O1 with purified recombinant B-subunit of cholera toxoid. It has to be administered in two doses about one week apart. It confers, as shown in field trials in Bangladesh, Peru and Mozambique, 60–85% protection for six months in young children and about 60% in older children and adults after two years [6-8]. Longini Jr. et al. [9] used data collected in 1985–1989 from a randomised controlled OCV trial in Bangladesh to calculate reductions of cholera cases. Their model indicated that a 50% coverage with OCV would lead to a 93% reduction in the entire population while a lower coverage of 30% would still reduce the cholera incidence by 76%.

### Global and local burden of cholera

Cholera is mainly endemic in low-income countries in Africa, Asia, Central and South America. A total of 177,963 cases and 4,031 deaths, corresponding to a CFR of 2.3%, have been reported to WHO in 2007 with Africa having the largest share of worldwide reported cholera cases (94%) and deaths (99%) [10]. This share of officially reported cases from Africa has increased considerably from 20% in the 1970s to 94% in the period 2000–2005 while the Asian share has simultaneously dropped from 80% to 5.2% over the same three decades [11]. There is a similar picture with regard to reported deaths: Africa's share has increased from 22% to 97%, and Asia's has showed a steep decline from 77% to 2.4%. It has to be noted, however, that these official figures do not reflect the true burden of cholera since serious under-reporting due to technical (surveillance system limitations, problems with case definition and lack of standard vocabulary) and political (fear of travel or trade sanctions) reasons are suspected [10]. Zuckerman et al. [12] identified mainly under-reporting from the Indian subcontinent and Southeast Asia in a review carried out in 2004.

In Zanzibar, where this study will be conducted, a cholera outbreak with 411 cases and 51 deaths was reported for the first time in 1978 from a fishermen village [13]. Thirteen outbreaks followed since then with almost annual episodes since the year 2000, with case-fatality rates ranging from 0% to 17% and showing a downward trend over the last two decades (Reyburn et al., unpublished data). During the last outbreaks in 2006/2007, 3,234 cases and 62 deaths were reported (CFR: 1.9%). A seasonal pattern can be observed that follows the rainy seasons (usually from March to June and from October to November) during which widespread flooding occurs frequently. Such deteriorating environmental conditions subsequently expose the majority of inhabitants on both islands to an increased risk of water-borne diseases due to the scarcity of safe drinking water supplies and a generally poor or lacking sanitation infrastructure in periurban and rural areas.

Despite all efforts in the past and the inexpensive and relatively easy use of ORS as major treatment [14], cholera still poses a serious public health problem in low-income countries. Thus, a concerted action is needed to control cholera and to mitigate its health-related and economic consequences not only by maintaining and improving existing measures like water supply, sanitation and hygiene behaviour but also by assessing new prevention options like OCV mass vaccinations of vulnerable populations [5,12,15].

### Importance of sociocultural and behavioural research on vaccine introduction

Public health interventions to reduce disease burden must take into account the local realities to achieve a sustainable benefit for the affected populations. Solely relying on prevention or treatment measures that proved to be suitable in a given context does not necessarily make it appropriate for other situations.

Vaccination programmes have suffered a reduced coverage (e.g. rumours about tetanus toxoid causing infertility in Tanzania [16]) or were even brought to a halt because of an ignorance of local realities (e.g. Northern Nigerian resistance to polio vaccination [17,18]). Other interventions, especially when implemented in a top-down approach, experienced the same difficulties [19-21].

To ensure the success of vaccination campaigns, a vaccine should not only be efficacious, relatively trouble-free for patients in its administration and preferably also cost-effective, but it is equally important that implementers consider community-held ideas, fears and individual help-seeking behaviour regarding the infectious disease and the vaccine of interest [22,23].

Infrastructure, logistics, politics, and social and cultural features were identified as significant factors which determine vaccine acceptance and thus the success or failure of immunisation programmes in low-income countries [24-26]. The importance of the social and cultural context on vaccine acceptance was assessed in various recent studies for typhoid fever and shigellosis (e.g. in Asian countries [27-31]). It was reasserted that the importance of the social and cultural context on vaccine introduction has to be studied carefully in order to improve vaccination coverage [32].

Research to improve the health of people needs to include gender issues since they play a crucial role in health and health planning [33]. Gender differences are context-specific and thus require that sociocultural and behavioural research be done to complement clinical or epidemiological research. A recent review on the control of tropical diseases concluded that more detailed data about illness experience, meaning and help-seeking behaviour is needed on the gender level to inform the planning and execution of health interventions [34].

Socioeconomic features, and cultural beliefs and practices, may vary across and within different sites or populations. And since differences in income, education, neighbourhood, infrastructure, etc. can affect people's health and behaviour regarding risk and relief, it is prudent to include site-specific analyses when doing research on the acceptance of community vaccine interventions.

### Protocol review and ethical clearance

This paper summarises the protocol that had been reviewed by two independent scientists with expertise in the field of cholera and social science research before it was submitted to and accepted by the WHO Research Ethics Review Committee and the Ethics Committee of Zanzibar.

All participants will be informed about the study and individual written consent obtained before conducting discussions or interviews. All data will be handled with strict confidentiality and made anonymous before analysis.

### Rationale for research: socioeconomic and behavioural (SEB) study

In late 2006, WHO received a grant from the Bill and Melinda Gates Foundation to work on the pre-emptive use of OCV in vulnerable populations at risk. The main focus of this grant is to examine how OCV can sustainably be used in countries with endemic cholera in addition to usually recommended control measures such as provision of safe water, adequate sanitation and health education. An important feature of the project is to collect evidence to assess the usefulness and financial stability of establishing an OCV stockpile.

To achieve these goals, WHO launched a joint venture with the Ministry of Health and Social Welfare of Zanzibar (MoHSW) to vaccinate 50,000 community residents older than two years living in communities at high risk of cholera with Dukoral^®^. The two islands of Zanzibar (Figure 1) were chosen as study area since they have been regularly affected by cholera over the past three decades and since the local government wishes to enhance its strategy to control the disease and to examine the possibility of introducing OCV as a public health measure.

Complementary to the vaccination campaign, since no sociocultural and behavioural studies related to cholera and OCV introduction have been conducted yet in African settings, the SEB study was conceived as a pilot project to address the research questions stated below. Besides the focus on cholera, it was also decided to include, to a lesser extent, shigellosis (bloody dysentery caused by *Shigella spp*.) in this research to investigate similarities and differences between the community perceptions of these two serious and potentially fatal diarrhoeal diseases.

### Aims and research questions

The main aim of the SEB study, its stakeholders and research questions are as follows:

To generate evidence on the role socioeconomic and sociocultural factors can play to inform government policies regarding the introduction of OCV as part of a sustainable and financially viable cholera control strategy.

To inform the Government of Zanzibar, in particular the Ministry of Health and Social Welfare, regarding the national policy on cholera control and the use of OCV on the archipelago.

#### Stakeholders

Research will be done on the following four stakeholder levels in Zanzibar:

- Level I: policy makers on national and regional level

- Level II: allopathic and traditional health care providers working in the target areas and district hospitals

- Level III: formal and informal local government and community leaders and teachers from the target areas

- Level IV: adult community residents (household level)

#### Research questions

In populations where cholera is endemic:

- What are the perceptions of cholera in the context of diarrhoeal diseases, in particular shigellosis?

- What are the essential features of cholera and shigellosis?

- What is the acceptance of OCV?

For each question, the following comparisons will be made between:

- Gender

- Site: periurban (Unguja) vs. rural (Pemba)

- Vaccination (intervention) status

- Stakeholders: all four levels

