## Methods and design

### Study setting

Zanzibar consists of two major islands, Unguja (also named Zanzibar) and Pemba. They are situated in the Indian Ocean about 40–60 km off the coast of Tanzania and a few degrees south of the equator (Figure 1). In 1964, shortly after independence from the colonial powers, the archipelago and Tanganyika formed the United Republic of Tanzania. Zanzibar as a semiautonomous entity within Tanzania consists of five regions which are subdivided into ten districts, 50 constituencies and 296 communities (Shehias). The main islands cover approximately 2,557 km^2 ^(Unguja: 1,651 km^2^, Pemba 906 km^2^). They are inhabited by a population of approximately 985,000 (in 2002) with Unguja having a share of 63% and Pemba of 37%. The inter-censal annual growth rates (1988–2002) varied from 2.1 to 4.5% [35]. Its mainly Islamic inhabitants are speaking Kiswahili. One-fourth of the population has not received any education and the primary education net enrolment ratio amounts to 77% [36].

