#### Target areas

The SEB study will take place in the periurban Shehia of Chumbuni (population estimate: ca. 13,500) in Unguja and the rural Shehia of Mwambe (population estimate: ca. 8,500) in Pemba. These two Shehias represent core areas of the mass vaccination campaign and were selected based on epidemiological data collected from recent cholera outbreaks (Reyburn et al., unpublished data) [13]. The selection of Chumbuni and Mwambe as target areas for the SEB study was therefore based on epidemiological vulnerability criteria (i.e. attack rates) and not on socioeconomic status.

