##### Sample size calculation for EMIC interviews

The following calculations are based on a 95% significance level and 80% power. The prominence means of the different categories of cultural epidemiological variables will be compared in bivariate analyses (by site, gender, anticipated vs. actual vaccination status) and tested for significant differences using the Wilcoxon rank-sum test. To detect a difference of 0.5 between prominence means with equal standard deviations of 1.5, a sample size of 164 for each group is required. The calculation is based on a two-sample t-test assuming a worst-case scenario, i.e. no underlying distribution in the data, which requires that the sample size derived from the t-test (n = 142) be divided by 0.864 which equals 164.4 [44]. Hence, the overall sample size (two groups per phase times two phases) will be 656, with a sample size of 328 per phase.

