## Discussion

The study will clarify local perceptions of cholera and show how these and socioeconomic factors affect anticipated and actual acceptance of oral cholera vaccine in Zanzibar. The cross-sectional design and mixed-methods approach, attentive to the interests of various stakeholders, will help to explain critical practical features of cholera control. Cultural factors are widely regarded as important determinants of vaccine acceptance, but difficult to study. This study has formulated an approach that enables systematic consideration of their influence. Our findings and experience will guide the programme in Zanzibar. They will also show how research may enhance the effectiveness of interventions for cholera and other health problems in various settings where sociocultural and socioeconomic factors influencing population behaviour require careful study.

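### The site comparison labelled periurban versus rural has one Shehia of each type, each on a different island, so it can show only that Chumbuni and Mwambe differ

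*Protocol article*

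**What the plan says.** Under Research questions, the Protocol article lists four comparisons to be made for each question. One of them is "Site: periurban (Unguja) vs. rural (Pemba".

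Under Target areas it fixes where the data come from: "The SEB study will take place in the periurban Shehia of Chumbuni (population estimate: ca. 13,500) in Unguja and the rural Shehia of Mwambe" in Pemba. The choice of these two was "based on epidemiological vulnerability criteria (i.e. attack rates) and not on socioeconomic status". Under Study setting, Zanzibar is described as having "five regions which are subdivided into ten districts, 50 constituencies and 296 communities (Shehias".

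Under Sample size calculation for EMIC interviews, prominence means are to be compared "by site, gender, anticipated vs. actual vaccination status", and the sample is sized as a two-group comparison of individual respondents. The Sampling lists for phases 1 and 2 then give 164 adults per site and 328 per phase, drawn at random within the two target areas.

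The section Level IV: quantitative data tests differences at p ≤ 0.05. For the acceptance models it keeps variables with a bivariate p ≤ 0.3 and passes them to stepwise logistic regression. Site is not named as a variable that stays in the model.

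The reason given for looking at sites, under Importance of sociocultural and behavioural research on vaccine introduction, is that "it is prudent to include site-specific analyses when doing research on the acceptance of community vaccine interventions".

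**The concern.** The label names a contrast between two kinds of residence, but the design has one community of each kind. Anything that differs between Chumbuni and Mwambe (island, outbreak history, local leadership, how the campaign was delivered) goes with the periurban/rural label and cannot be told apart from it. Each site also has its own three interview teams working at the same time. Unless teams rotate between islands, which the article does not say, interviewer differences go with site too. That could matter for prominence scores, which depend on whether an answer was spontaneous or probed.

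The study is meant to inform national policy on oral cholera vaccine. A result reported under a periurban/rural heading invites use in other Shehias of each type, and these data give no measure of how much Shehias of one type differ among themselves.

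A related gap sits in the acceptance models. Site is a sampling stratum, with equal numbers taken from populations of about 13,500 and 8,500. Under the p ≤ 0.3 screen and stepwise selection it could nevertheless drop out of the model.

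**Working it through.** **1. The plan's own figure.** The inputs, from the sample size section, are a difference of 0.5, an SD of 1.5 in each group and the error rates in "The following calculations are based on a 95% significance level and 80% power". I read these as a two-sided 5% test, because sidedness is not stated.

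- n per group = 2 × (1.96 + 0.842)² × 1.5² / 0.5² = 141.3, rounded up to 142. This matches the plan.
- 142 / 0.864 = 164.35. The plan prints 164.4 and uses 164, so the figure reproduces.
- Power for a 0.5 difference at 164 per group, with efficiency 0.864, is 80%.

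This is a sound calculation for a difference between the adults of two named communities.

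**2. What the design identifies.** The household survey fills two of the four possible cells:

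| | Unguja | Pemba |
|---|---|---|
| Periurban | Chumbuni | none |
| Rural | none | Mwambe |

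The indicators for residence type, island and Shehia are the same variable, so no regression can separate them. With one Shehia per type there are zero degrees of freedom for variation between Shehias within a type, and the study cannot estimate that variation. The preparatory focus groups draw on adjacent Shehias, but they are qualitative and add no survey data to this contrast.

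**3. What happens if the test is read as one of residence type.** Suppose each Shehia were a random draw from its type, with between-Shehia ICC ρ and m = 164 respondents.

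- Respondent-level SE = 1.5 × √(2/164) = 0.166.
- The true variance of the difference is larger by the design effect DE = 1 + (m − 1)ρ.
- True type I error = 2 × [1 − Φ(1.96/√DE)].
- Effective sample size per type = m/DE, which can never exceed 1/ρ.

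The article gives no ICC, so the values of ρ are assumptions:

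| Assumed ρ | DE | Type I error | Effective n per type | Ceiling 1/ρ |
|---|---|---|---|---|
| 0.001 | 1.16 | 0.07 | 141 | 1000 |
| 0.005 | 1.81 | 0.15 | 90 | 200 |
| 0.01 | 2.63 | 0.23 | 62 | 100 |
| 0.02 | 4.26 | 0.34 | 38 | 50 |
| 0.05 | 9.15 | 0.52 | 18 | 20 |

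**4. More respondents do not help.** Pooling the two phases gives 328 per site. At ρ = 0.01, DE = 1 + 327 × 0.01 = 4.27 and the type I error for the residence reading rises from 0.23 to 0.34. Only further Shehias of each type would give information on that question.

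**The case against.** The strongest reply is that the planned factor is site. Setting and island are both stated openly in the label, the rationale speaks of site-specific analyses, the sample size section tests by site, and residents are sampled at random within each Shehia. For a contrast of two named sites, the respondent-level test is the right one. That stands: neither the sample size nor the test is in error.

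Several stronger readings are tempting, and the article does not support them.

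- A reader might infer that a site difference will be reported as a periurban/rural determinant of acceptance. No section says so; the passage on determinants does not name site or residence at all.
- A reader might infer that the false-positive rate of the planned comparison is far above 5%. For the site contrast, between-Shehia variation causes no such inflation. The figures above apply only to an inference to periurban and rural Shehias in general. They rest on assumed ICCs, and at 0.001 the error is only about 7%.
- A reader might see selection on attack rates as the source of the confounding. It was applied to both Shehias, it is disclosed, and it matches the high-risk population that the campaign targets. It limits generalisation; the aliasing comes from having one Shehia per type.
- A reader might take the Discussion's aim, to show how perceptions and socioeconomic factors "affect anticipated and actual acceptance of oral cholera vaccine in Zanzibar", as a claim to represent the whole archipelago. The article's abstract places the work in communities at high risk of outbreaks, the rationale calls it a pilot, and national representativeness is nowhere claimed.

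It can also be said that a condensed article leaves interpretive limits to the full protocol. But the label and the two-site design are both stated here, and no later analysis plan can supply missing Shehias.

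**Conclusion.** The point holds as a matter of labelling and interpretation. The aliasing of residence type, island and community is complete. It follows from the Target areas section alone and needs no assumed figure. The tests support the statement that Chumbuni and Mwambe differ, and nothing more general about residence or island.

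The size of the error under a residence reading is unknown. The 7% to 52% range is illustrative: it assumes ICCs from 0.001 to 0.05, a two-sided 5% test, and Shehias treated as random draws from their type, which these two were not. Misreporting is a risk that the label creates; it is not something the plan commits to. Because the remedy is nearly free and bears directly on what can be concluded for policy, it is worth making.

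**What to change.** 1. Under Research questions, restate the comparison as Chumbuni (periurban, Unguja) versus Mwambe (rural, Pemba).
2. Add one sentence saying that effects of residence, island and community cannot be separated in this design, and that a difference will be reported as one between these two high-attack-rate communities.
3. In the acceptance models under Level IV: quantitative data, keep site as a fixed adjustment factor regardless of the p ≤ 0.3 screen and the stepwise selection. Its coefficient may be reported as a site difference, but not as an effect of periurban or rural residence.

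The cost is a narrower claim and one model term, with no new data. Site differences remain available for local planning, which is what the article's own rationale asks for. A genuine periurban/rural comparison would need several Shehias of each type on each island, which is a different and larger study.
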